# DREAM: an adaptive, randomised, placebo-controlled trial of duloxetine for reducing leg pain in people with chronic sciatica—trial protocol

**DOI:** 10.1136/bmjopen-2024-096796

**Published:** 2024-12-31

**Keywords:** Neurological pain, Chronic Pain, Clinical trials, Musculoskeletal disorders

## Abstract

**Introduction:**

Sciatica is a debilitating condition that often becomes chronic, and for which there are few effective treatment options. Treatments such as the anti-depressant duloxetine have shown promise, but the evidence is inconclusive. We are describing a high quality, definitive trial to investigate the efficacy, safety and cost-effectiveness of duloxetine in chronic sciatica.

**Methods and analysis:**

The duloxetine for chronic sciatica (DREAM) trial is a randomised, superiority, parallel-group, placebo-controlled, triple-blinded (participant, clinician, assessor) trial with an adaptive group sequential design investigating the efficacy and safety of duloxetine in participants with chronic sciatica of at least 3 months duration. Participants will be randomised at a 1:1 ratio to duloxetine or placebo. 332 participants will be recruited on presentation to general practices, specialist clinics and hospital emergency departments or from hospital in-patient wards and from the community. In the active treatment group, participants will receive duloxetine 60 mg per day for 12 weeks, including 1 week of titration at 30 mg/day. The treatment phase will be followed by a 2-week tapering phase where they will receive duloxetine 30 mg/day. Participants will be followed-up for 1 year, with outcomes being measured 4, 8, 12, 16, 26, and 52 weeks post-randomisation. The primary outcome is leg pain intensity at 12 weeks post-randomisation. Secondary outcomes include back pain intensity, disability, time to recovery, quality of life, depressive and anxiety symptoms, and sleep disturbance. Adverse events will be recorded, and a cost-effectiveness analysis will be conducted.

**Ethics and dissemination:**

Ethical approval has been granted by the University of Sydney Human Research Ethics Committee. Trial results will be disseminated by publications, conference presentations and via the media.

**Trial registration number:**

ACTRN12624000919516.

STRENGTHS AND LIMITATIONS OF THIS STUDYDREAM is a two arm, triple-blinded (participant, clinician and assessor) randomised controlled trial of duloxetine compared with placebo for reducing leg pain in patients with chronic sciatica.DREAM uses an adaptive group sequential design with two interim analyses.Despite blinding of the study medication, there is a risk that participants may suspect they were randomised to the active treatment arm given the known adverse effects of duloxetine (eg, nausea, dry mouth).

## Introduction

Sciatica is the common term used to describe painful lumbosacral radiculopathy. It is clinically defined as pain that radiates down the leg in a dermatomal distribution and is accompanied by neurological deficits (eg, sensory loss, weakness or reflex loss) in the corresponding dermatomal or myotomal distribution.^1 2^ Sciatica is typically considered to have a favourable prognosis, but this assumption is not supported by evidence.^3^ Half of those who develop sciatica do not improve after 1 year; and, for nearly 40% of these, their persistent pain is of at least moderate intensity.^4^ The burden of sciatica is also disproportionally high compared with those with back pain only. People with sciatica have more pain and disability, poorer quality of life and use more healthcare resources than those with back pain only.^5^

Pharmacological treatments are a common component of the clinical management of sciatica.^6 7^ However, the most used pharmacological treatments for sciatica are either known to be ineffective or their effectiveness is unclear. For example, while opioid analgesics are the most commonly used pain relieving medicine for sciatica, their efficacy for sciatica is uncertain and opioid-related harms may outweigh their benefits.^8^ Non-steroidal anti-inflammatory drugs have small effects on pain compared with placebo for acute sciatica,^9^ but there are no trials in chronic sciatica,^10^ and their use increases the risk of vascular and gastrointestinal events.^11^ Anti-convulsants (eg, pregabalin) are commonly used, but these medicines are reported to be ineffective for managing sciatica.^12 13^

Anti-depressants are commonly used to treat chronic sciatica, but the evidence is inconclusive.^14 15^ In a 2021 systematic review, we found evidence suggesting that some anti-depressants, such as those from the serotonin-noradrenaline reuptake inhibitor (SNRI) class, may be effective for chronic sciatica and provide clinically worthwhile reductions in pain.^15^ However, estimates were based on three small (n=96), low-quality trials, and the certainty of evidence ranged from low to very low. Of the SNRI anti-depressants investigated for the management of sciatica, duloxetine appears to be the most promising. Duloxetine has been shown to be effective for the largest number of conditions among all other anti-depressants^14^ and is better tolerated than other anti-depressants commonly used for chronic pain conditions.^16^,^19^ Unlike opioids, duloxetine use has not been associated with the risk of misuse and addiction.^20^

Duloxetine is a potent inhibitor of serotonin and norepinephrine uptake, two key neurotransmitters involved in pain modulation.^21 22^ The analgesic effect of duloxetine has been attributed to both central and peripheral mechanisms based on research in animal models.^18^ These studies suggest a central mechanism that is rapid and requires descending noradrenergic inhibitory controls from the brain to the spinal cord plus a peripheral mechanism that is delayed and relies on the anti-neurogenic inflammation properties of duloxetine.^18^ The ability of duloxetine to reduce neurogenic inflammation makes it a promising pharmacological treatment for sciatica, a condition characterised by neuropathic pain.^23^ Duloxetine is also a low-cost treatment. For example, in 2024, the out-of-pocket cost in Australia for a 12 week treatment regimen of 60 mg per day followed by 2 weeks of tapering at a dose of 30 mg per day is estimated to be as low as $A91 (calculated based on dispensed price of 3×28 APO-Duloxetine 60 mg enteric capsules and 1×28 APO-Duloxetine 30 mg enteric capsules).^24 25^ Although not currently approved by the Therapeutic Goods Administration in Australia for the treatment of back pain, anti-depressants are commonly prescribed ‘off-label’ for back pain.^26^

To resolve the current uncertainty, we plan to conduct the duloxetine for chronic sciatica (DREAM) trial, a randomised placebo-controlled trial to investigate the efficacy and safety of duloxetine for chronic sciatica. The DREAM trial will provide high-quality evidence on the efficacy of duloxetine for sciatica, addressing a key research priority in the field.^27^

The primary aim of DREAM is to investigate the efficacy of duloxetine, compared with placebo, on leg pain intensity in people with chronic sciatica. The secondary aims are to investigate its efficacy in improving other key patient reported outcomes (including low back pain, disability, quality of life, symptoms of depression, anxiety and sleep disturbance) and its safety and cost-effectiveness in this indication.

## Methods and analysis

### Design

DREAM is a randomised, superiority, parallel-group, placebo-controlled, triple-blinded (participant, clinician, assessor) trial with an adaptive group sequential design. DREAM was designed to investigate whether taking 60 mg of duloxetine daily for 12 weeks can reduce leg pain intensity in individuals with chronic sciatica. The trial has been prospectively registered on the Australia and New Zealand Clinical Trials Registry (ACTRN12624000919516). This paper details the trial protocol and follows the Standard Protocol Items: Recommendations for Interventional Trials 2013 Statement recommendations.^28^

### Study setting and identification of participants

The DREAM trial will be conducted across various healthcare settings, including general practices, specialist outpatient facilities (such as rheumatology clinics), hospital emergency departments and inpatient wards. Registered medical practitioners will be invited to participate as study doctors. Participants will be screened and, if eligible, recruited to the study when they are seen by a participating study doctor. Potential participants will also be identified through community advertising (eg, on social media). These participants will be referred to a study doctor to be screened and, if eligible, recruited to the study. Regardless of the clinical setting, all study sites will follow the same study procedures. Consultations with the study doctor may be face-to-face or via telehealth. The potential recruitment pathways are shown in figure 1. Participant recruitment is expected to run between December 2024 and June 2027 with the final follow-up assessment in June 2028.

**Figure 1 F1:**
[figure not shown]
Recruitment pathways ED, emergency department; GP, general practitioner.

### Eligibility criteria

Adults living with chronic sciatica will be screened for eligibility by a study doctor. A screening form will be completed for each potential participant to confirm eligibility for the study. Eligibility criteria are described in box 1.

Box 1Eligibility criteriaInclusion criteriaAdults (≥18 years) with radiating pain into one leg in a dermatomal distribution.Leg pain duration of at least 3 months.Evidence of nerve root involvement, defined by the presence of at least one of the following clinical signs in the corresponding distribution: myotomal weakness and/or diminished reflex and/or sensory deficit and/or imaging evidence of nerve root impingement that is consistent with the clinical presentation.Leg pain that is at least moderate in intensity at the time of enrolment by a study doctor (as measured by a modified version of item 21 in the 36-Item Short Form Survey Instrument).An adequate understanding of English or the availability of interpretation services for the participant to complete the trial.Exclusion criteriaKnown or suspected malignancy or specific pathologies in the spine (eg, fracture, cauda equina syndrome).Having had spinal surgery or an interventional procedure (eg, epidural injection) in the preceding 6 months.Scheduled to have a spinal procedure (eg, spinal surgery, epidural injection) within 12 weeks at the time of enrolment.Currently taking (or taken in the last 2 weeks) any anti-depressant for any condition.Any contraindications to duloxetine: known hypersensitivity to duloxetine, known acute or chronic liver disease, concomitant use with CYP1A2 inhibitors (eg, fluvoxamine) or concomitant use of monoamine oxidase inhibitors (eg, moclobemide), or use that has ceased less than 2 weeks ago.Known history of chronic kidney disease stage 4 or above.Precautions for use of duloxetine as specified by the Product Information where risks outweigh potential benefits (eg, depressive symptoms for which treatment is required as judged by the study doctor, bipolar disorder, history of seizure disorder, etc).Previous severe adverse reaction to duloxetine (eg, serotonin syndrome) as judged by the study doctor.For females: pregnancy, breastfeeding or planning conception during the treatment period.

### Participant timeline

Participants will have an initial consultation with their study doctor and up to two follow-up consultations, if required. These follow-up consultations can happen anytime from week one post-randomisation to week 14 post-randomisation. The participant timeline is shown in figure 2.

**Figure 2 F2:**
[figure not shown]
Participant timeline

### Assignment of interventions: allocation/randomisation

An independent statistician not involved in any other aspect of the study will generate the randomisation sequence a priori using a computerised random number generator. Random allocation to either duloxetine or placebo will occur in a 1:1 ratio using randomly permuted blocks of various sizes. Study medication packs will be manufactured and labelled according to the randomisation sequence by the investigational medicinal product management company, Syntro Health. Medication packs will be allocated to the various recruitment settings (ie, general practice or specialist clinics, hospital or community) in complete block sizes. The study medication packs will be dispensed direct to the participant via a central pharmacy service provided by Syntro Health, except for those participants recruited from the hospital setting whose study medication will be dispensed via the hospital’s clinical trials pharmacy. The study medication packs will be dispensed sequentially from within the blocks allocated to the respective recruitment setting.

The participant will be enrolled into the study after the informed consent process has been completed and the participant has met all inclusion criteria, and none of the exclusion criteria and study medication has been prescribed for them. The participant will be dispensed a study medication pack with a unique study enrolment number. Randomisation will occur when the medication pack is allocated to the participant during dispensing.

### Blinding

Allocation to treatment group will be concealed, and the active and placebo medicines will be identical in appearance and taste, ensuring blinding of the participant, study doctor, assessor and all study personnel including the research team and the steering committee. We will measure the success of blinding by asking participants to guess their group allocation at the end of the treatment period.

To maintain the overall quality and rigour of the study design, unblinding should only occur in exceptional circumstances when knowledge of the actual treatment is essential for further clinical management of the participant, such as with Serious Adverse Events. The decision to unblind a participant will be made in consultation with the clinicians involved in the participant’s management (including the study doctor), the independent Medical Monitor, and the Steering Committee.

If unblinding is deemed to be necessary, the study team will facilitate contact between the clinicians involved in the participant’s management and the independent statistician who generated the randomisation sequence, and care will be taken to ensure that only the study personnel who will be involved in further management of that participant will be unblinded. Unblinding will not necessarily be a reason for the participant to discontinue the study.

After the final participant has completed the study, the study doctors, research team and Steering Committee will remain blinded until the data analysis and interpretation is complete.

### Intervention

Participants in both groups will receive guideline-recommended advice from their study doctor, consisting of information on the nature of sciatica, its prognosis, encouragement to continue with normal activities, importance of avoiding bed rest and to avoid opioid medicines.^27 29^ To ensure consistency in how advice is delivered, study doctors will be trained in the study protocol and receive ongoing support from research team throughout the trial.

#### Study medication

Study participants will be provided with the blinded study medication pack containing either the active study medication (duloxetine 30 mg enteric-coated capsules) or matching placebo capsules manufactured and labelled to Good Manufacturing Practice standard by Syntro Health (Victoria, Australia).

Participants randomised to the active arm of the study will receive a 12-week course of oral duloxetine followed by a 2-week tapering phase. The starting dose will be duloxetine 30 mg/day for 1 week (one 30 mg capsule per day), increasing to 60 mg/day for 11 weeks (maintenance phase: two 30 mg capsules per day). In the 2-week tapering phase, they will receive 30 mg/day (one 30 mg capsule per day) for 2 weeks before treatment is discontinued.

The duloxetine regimen of 60 mg one time per day was chosen as it is the recommended dose for chronic pain and diabetic peripheral neuropathic pain.^30^ There is no evidence, including evidence from our review,^15^ that higher duloxetine doses (eg, 120 mg/day) confer additional benefits, but they do increase the incidence of adverse events and treatment discontinuation.^30^ The 12-week duration of the treatment is consistent with that reported in trials of duloxetine for other pain conditions.^14^ A 2-week tapering period is consistent with recommendations for the Australian population to minimise the risk of withdrawal symptoms.^20^

Participants randomised to the placebo arm of the study will receive the equivalent number of matching placebo capsules throughout the 14 weeks of the treatment phase.

Participants will be contacted by telephone at weeks 2, 6 and 12 by a blinded research team member to monitor treatment and collect adverse events data. This researcher, who will have nursing or pharmacy qualifications, may recommend participants to visit their study doctor for dose modification if they are experiencing troublesome adverse events or there are concerns regarding the participant’s safety. The responsible researchers will be trained and provided guidance regarding events and concerns that should receive medical attention. Study doctors, who also remain blinded, may make modifications to the treatment regimen if required. Changes and a justification for the changes will be noted in a treatment monitoring form. Participants will be allowed two follow-up visits to their study doctor during the active treatment phase, if required.

Participants experiencing adverse effects will be allowed to reduce the dose of study medication in the treatment phase to one capsule per day (30 mg/day in the duloxetine arm) if considered appropriate by the study doctor. Likewise, if confirmed by their study doctor, participants will be allowed to start the tapering phase earlier if they recover before the 12-week period is completed. Recovery is defined as seven consecutive days with leg pain intensity ≤1 out of 10. Duloxetine dose escalation above 60 mg per day is not permitted in this trial.

Once a participant has given informed consent and has been recruited to the trial, a prescription will be sent electronically to the central pharmacy at Syntro Health. The central pharmacy will dispense and dispatch the study medication packs direct to the participant’s preferred address. Medication packs will be dispensed in sequential order. Randomisation occurs when the study medication pack is assigned to a participant during dispensing. The medication pack will include four bottles of blinded study medication: three bottles each containing 54 capsules and one bottle containing 14 capsules, plus a copy of the consumer medicines information leaflet for duloxetine. The smaller bottle will be designated for the 2-week tapering period. The medication pack and individual bottles will be labelled in accordance with labelling requirements for investigational medicines in Australia. In addition, the labels will include instructions on when to increase and decrease the number of capsules taken per day.

To monitor compliance with the study medication regimen, study doctors will be asked to confirm the study medication prescribed, and participants will be asked to record their intake in a daily diary. On cessation of treatment either at 14 weeks or earlier, if appropriate, participants will be asked to return any unused medicines to the research team for counting using a prepaid satchel.

#### Concomitant treatments

All participants may receive additional care during the treatment period as deemed appropriate by their study doctor. This may include physical or manual therapies or other medications except other anti-depressants or medications that should not be used in combination with duloxetine. Study doctors will be recommended to refrain from scheduling interventional procedures during the 14-week treatment period.

Participants will be advised that they should not commence any prescription medicine while they are taking the study medication without discussion with the study doctor. This provision does not apply if urgent pharmacotherapy is required in a medical emergency.

To minimise the risk of inappropriate concomitant treatments (eg, medicines that also have a serotonergic effect and that could increase the risk of serotonin syndrome. eg, tramadol, or potent inhibitors of CYP1A2, eg, ciprofloxacin), participants will be issued a Study ID card which they should present to their treating healthcare practitioners. The card will indicate the participant is receiving blinded study medication which may be duloxetine. The card will include the research team’s contact details.

We will record the use of all concomitant medications for sciatica, including analgesic medications, at each follow-up survey. Participants will be allowed to use concomitant analgesia provided the medication is not contraindicated with duloxetine.

### Outcomes

The outcomes for this study were informed by a core set of outcomes recommended for back pain trials and consultation with consumers.^31 32^ Outcome measures, unless otherwise stated, will be collected by questionnaire at baseline, 4, 8, 12, 16, 26 and 52 weeks.

#### Primary outcome

The primary outcome is leg pain intensity (average intensity over the past 24 hours) measured on a 0–10 numerical rating scale (NRS). The primary timepoint is at week 12, when the participant will have completed 12 weeks of treatment and is about to commence tapering of the study medication.

#### Secondary outcomes

The key secondary outcome is disability measured by the Roland Morris Disability Scale for Sciatica.^33^

The following will also be recorded as secondary outcomes:

Low back pain intensity (average intensity over the past 24 hours) measured on a 0–10 NRS.Time to recovery measured by a pain diary. Participants will be asked to record the average daily leg pain score in a pain diary for the duration of the treatment period using the 0–10 NRS. Recovery is defined as seven consecutive days with leg pain intensity ≤1 out of 10. Data will be censored at 14 weeks or if participants meet the definition of recovery, whichever occurs first. If recovery has not occurred by 14 weeks, participants will be asked at subsequent follow-up assessments (26 and 52 weeks) whether they have recovered or not and the recovery date (if available).Health-related quality of life measured by the EQ-5D-5L, an instrument developed by EuroQol which assesses 5 dimensions of health with 5 levels of severity for each dimension.^34^Depressive symptoms measured by the Patient Health Questionnaire-9.^35^,^37^ This will be collected at baseline and week 8.Anxiety symptoms measured by the Generalised Anxiety Disorder 7-item.^38^ This will be collected at baseline and week 8.Sleep disturbance measured by the 8-item Patient-Reported Outcomes Information System Sleep Disturbance Short Form.^39^ This will be collected at baseline and week 8.Global perceived effect (GPE) scale. GPE is measured on a −5 (vastly worse) to +5 range (completely recovered).^40^

The following outcomes will also be recorded:

Adverse events (defined under the Harms section) will be collected by self-report at weeks 4, 8, 12 and 16 via the online or phone follow-up questionnaires. Additionally, the research team will contact participants by phone at weeks 2, 6 and 12 to assess whether they have experienced any adverse events in general and in particular whether they have experienced any of those on the 21-item Antidepressant Side-Effect Checklist.^41^Work absenteeism will be measured in a questionnaire collected at all time-points. Participants will be asked to estimate the number of days off paid work in the period since the previous follow-up survey with the following question: ‘In the last 4 weeks (*or period since the last study follow-up*), did you miss any days off your normal paid work due to your sciatica?’.^42^Adherence to study medication will be measured by the participants’ self-report of daily medication intake, as recorded in an online or paper diary, and by comparing the count of returned medications against the doctor’s prescription.Healthcare use, including healthcare consultations, diagnostic and therapeutic procedures, imaging and pathology services, and prescription medicines, will be collected using administratively linked data from the Australian Medicare Benefits Schedule (MBS) and Pharmaceutical Benefits Scheme (PBS), respectively, and each follow-up questionnaire.

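### The censoring rule for time to recovery treats recovery, which is the event, as a reason for censoring, and gives participants who have not recovered no censoring time except week 14

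*Protocol article*

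**What the plan says.** All of this is in the protocol article. Under Secondary outcomes, the outcome is introduced as "Time to recovery measured by a pain diary". Participants are to "record the average daily leg pain score in a pain diary for the duration of the treatment period using the 0–10 NRS". The event is fixed: "Recovery is defined as seven consecutive days with leg pain intensity ≤1 out of 10". The censoring rule follows: "Data will be censored at 14 weeks or if participants meet the definition of recovery, whichever occurs first". Participants who have not recovered by then are followed further: "participants will be asked at subsequent follow-up assessments (26 and 52 weeks) whether they have recovered or not and the recovery date (if available").

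The Study medication section gives the length of the treatment phase, taper included: placebo participants receive "the equivalent number of matching placebo capsules throughout the 14 weeks of the treatment phase". The same section foresees that some participants will stop treatment before week 14.

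The Secondary analysis section gives a model for continuous outcomes and a test for adverse events. It gives none for time to recovery, so the sentence above is the only rule the article states for how this outcome is observed and censored. Disability is the key secondary outcome; time to recovery is one of the others.

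**The concern.** In a time-to-event outcome, a participant leaves the risk set either with the event or censored without it. The rule puts recovery on the censoring side. Taken at its word, it leaves nothing to estimate.

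The second difficulty is what the rule leaves for everyone else. It names two times, recovery and week 14, and takes whichever comes first. For a participant who has not recovered, that is week 14. If the diary ends in week 3, nothing is known after week 3, yet the rule as worded carries that person as unrecovered for another 11 weeks. This adds person-time in which a recovery could not have been recorded. If it happens more in one arm, that arm's recovery rate is pulled down.

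A smaller matter is that the role of recovery dates given at 26 and 52 weeks is not stated. Those dates come from participants' reports and not from the daily diary, so adding them to the diary data would change both the time horizon and the way recovery is measured.

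**Working it through.** The article gives no event count, hazard ratio or power for time to recovery, so there is no published figure to reproduce.

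**Step 1: events under the literal rule.** The maximum evaluable sample is 282 (Sample size section). The recovery rate by week 14 is not given, so a range is assumed.

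| Assumed recovery by week 14 | Events if recovery is the event | Events under the literal rule |
|---|---|---|
| 10% | 282 × 0.10 ≈ 28 | 0 |
| 20% | 282 × 0.20 ≈ 56 | 0 |
| 30% | 282 × 0.30 ≈ 85 | 0 |
| 40% | 282 × 0.40 ≈ 113 | 0 |

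**Step 2: effect of week 14 as the only censoring time.** Here recovery is counted as the event, and participants whose diary stops early are kept at risk to week 14.

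Assumptions (none is in the article, which gives only a 15% overall dropout allowance):
- exponential recovery times, with 30% placebo recovery by week 14;
- a fraction d of an arm stops the diary at a time S spread evenly over weeks 0 to 6, independently of recovery.

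Placebo hazard: λ = −ln(0.70)/14 = 0.02548 per week. With a true hazard ratio of 1.30, the duloxetine hazard is 0.03312.

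Formulas, per participant:
- Recoveries seen: (1−d)(1−e^(−14λ)) + d[1 − (1−e^(−6λ))/(6λ)].
- Person-weeks, held to week 14: (1−d)(1−e^(−14λ))/λ + d × the mean over S of [(1−e^(−λS))/λ + (14−S)e^(−λS)].
- Person-weeks, censored at diary stop: as above without the (14−S)e^(−λS) term.

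True ratio 1.30, stopping 20% on duloxetine and 8% on placebo:
- Placebo recoveries: 0.92 × 0.3000 + 0.08 × 0.0727 = 0.2818.
- Duloxetine recoveries: 0.80 × 0.3710 + 0.20 × 0.0931 = 0.3154.
- Placebo person-weeks, held: 0.92 × 11.775 + 0.08 × 13.124 = 11.883.
- Duloxetine person-weeks, held: 0.80 × 11.203 + 0.20 × 12.877 = 11.538.
- Rate ratio, held: (0.3154/11.538)/(0.2818/11.883) = 0.02734/0.02371 = **1.15**.
- Rate ratio, censored at diary stop: (0.3154/9.524)/(0.2818/11.062) = 0.03312/0.02548 = **1.30**, the true value.

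True ratio 1.00, same stopping:
- Duloxetine recoveries: 0.80 × 0.3000 + 0.20 × 0.0727 = 0.2545.
- Duloxetine person-weeks, held: 0.80 × 11.775 + 0.20 × 13.124 = 12.045.
- Rate ratio, held: 0.02113/0.02371 = **0.89**.

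A simulation with a Cox model on the same assumptions gave 1.14 and 0.89.

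**Step 3: range.** The same formulas with other stopping patterns (for the last row, 6 is replaced by 14):

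| Stopping, duloxetine v placebo | Stops spread over | True 1.30 becomes | True 1.00 becomes |
|---|---|---|---|
| 20% v 8% | 6 weeks | 1.15 | 0.89 |
| 18% v 12% | 6 weeks | 1.22 | 0.94 |
| 15% v 15% | 6 weeks | 1.30 | 1.00 |
| 20% v 8% | 14 weeks | 1.21 | 0.93 |

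The distortion comes from the imbalance between arms. With equal stopping it all but disappears.

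**The case against.** The strongest reply is that the meaning is plain in context. The outcome is called time to recovery, recovery is defined, and the next sentence speaks of those in whom it has not occurred by week 14. An analyst would take recovery as the event and read the sentence as saying when diary observation ends. This is largely right. It makes the fault one of wording and does not show that the analysis will be done wrongly. But a prespecified rule should not depend on the reader correcting it, and an SAP that counts recovery as the event would have to depart from this sentence.

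The second reply is that handling of incomplete diaries is ordinary SAP content, and the SAP is not shown. This also stands in part. A reader might infer that the trial intends to hold diary stoppers at risk to week 14; no text says so. Silence on diary stopping alone would be no finding. What can be said is that the stated rule offers a non-recovered participant no other censoring time.

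A reader might go further and conclude that the comparison is biased against duloxetine. The document does not support that. It gives no arm-specific stopping rate and no diary-completion rate, and stopping the capsules need not mean stopping the diary.

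A reader might also see a contradiction between closing the outcome at 14 weeks and asking about recovery at 26 and 52 weeks. The two can coexist, with the later answers as supplementary data; nothing says they will be pooled with the diary. Nor is the absence of a recovery question at week 16 an error. The Outcomes section lets individual measures depart from the general schedule, and this one does.

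**Conclusion.** The censoring rule is wrong as written: it classes the event as censoring, which read literally leaves 0 events where 28 to 113 of 282 would be expected at assumed recovery rates of 10% to 40%. This part rests on the text alone; the recovery rates only give it scale.

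The week-14 part is conditional. It needs the rule to be applied as worded and diary stopping to differ between arms. With 20% v 8% stopping over six weeks and 30% placebo recovery, a true hazard ratio of 1.30 is estimated as about 1.15 and a true 1.00 as about 0.89. With equal stopping there is essentially no bias.

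Severity is minor. Time to recovery is a non-key secondary outcome, and the primary analysis and sample size are untouched.

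**What to change.** Replace the censoring sentence in the protocol, and match it in the SAP, with wording such as: *Recovery (the first run of seven consecutive diary days with leg pain of 1 or less) is the event; participants without recovery are censored at their last completed diary day, at most week 14.* Add one sentence saying that recoveries reported at 26 and 52 weeks are summarised separately and do not enter the diary-based time-to-recovery analysis.

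Censoring at the last diary day still assumes that stopping the diary is unrelated to recovery prospects; the SAP is the place to address that.

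The cost is two sentences of text, with no new data collection and no change to treatment or visits. It should be done before unblinding, so that the definition cannot be chosen with results in view. A recovery question at week 16 would be an optional extra and is not part of this point.
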